**Fig. 9 Fig9:**
[figure not shown]
Interactions overview. Initial, daily, half-time, and final interaction within the intervention. After T_0_, the waitlist group will receive no further interaction until the intervention phase starts for this group, two weeks later with the interaction at the start of the intervention (T_1_). Note: T_0_: Assessment at baseline for control group only. T_1_: Start of intervention with start interaction and assessment. T_2_: Half-time of intervention with half-time interaction and assessment. T_3_: End of intervention with final interaction and assessment. Figure created by [name] as part of his employment at the Center for Digital Health Interventions

**Fig. 10 Fig10:**
[figure not shown]
MDMQ symptom and version of the day. Selection process of which symptom is chosen for the day. First (far left, top), the app draws randomly whether Mood, Agitation, or Anhedonia is measured on a given day. Second (second box, top), the app draws randomly whether version A or version B of the symptom drawn in step one is presented first. Third (third box, top), the participant interacts with Breeze. Fourth, the app presents the remaining version of the symptom drawn of the day. In the bottom part of the figure, different draws are illustrated. The first one illustrates that on a given day Mood was randomly chosen as a symptom. The random draw determines that version A is presented first, followed by version B after interacting with Breeze. Below this, further examples are illustrated

#### Incentive mechanism

Participants will receive financial compensation for their participation if they meet certain criteria. First, participants need to interact with the app at least once per day on 30 days and complete the daily trip with the intervention. The participants can use Breeze more often on any given day, but 30 different days are needed to complete the intervention and be eligible for compensation. Second, participants need to complete the additional questions at baseline (T_0_, waitlist control group only), the start of the intervention (T_1_), the half-time (T_2_), and the final assessment (T_3_) within the once-per-day guided interaction. Third, participants must complete the intervention in 30–45 days to receive a compensation of 40 CHF. Participants needing more than 45 days will not receive any financial compensation. Forth, participants completing the intervention in 30–40 days have the chance to win additional monetary compensation in a raffle (ten times 100 CHF, ten times 200 CHF, five times 300 CHF). Participants in the smartwatch group are not eligible for this raffle but can keep the smartwatch if they complete the intervention in 30-40 days. Since we are not collecting any personal information about the participants enforcing participants with insufficient data to return the smartwatch is not feasible. However, we strongly urge the participant in the final interaction to return the smartwatch if they did not provide sufficient data.

### Measurements and assessment times

Table 2 provides an overview of the measurements used at baseline (T_0_), the intervention’s start (T_1_), half-time (T_2_), the end of the intervention (T_3_), and during each daily interaction (Daily). We collect demographic data (age, gender, type of student, highest education level, occupation, or field of study) through open and multiple-choice questions at the start of the study.

**Table 2 Tab2:** Measurements used in the study at the different assessment times

Measurement	Screening	T0	T1	T2	T3	Daily	Objective
Pregnant, Resp., Card., mental disease	X	–	–	–	–	–	–
Demographics	–	–	X	–	–	–	–
*Distal outcomes*							
PHQ-9	X	X	X	X	X	–	2,3
GAD-7	X	X	X	X	X	–	2,3
TICS	–	X	X	X	X	–	2,3
*Proximal outcomes*							
MDMQ^1^	–	–	–	–	–	X	1,3
*Audio features*							
Voice commands	–	–	X^2^	X^2^	X^2^	X^2^	1,2
Breathing sounds	–	–	X^2^	X^2^	X^2^	X^2^	1,2
*Conversational agent*							
Reaction time to chatbot messages	–	X	X	X	X	X	1,2
Therapeutic alliance	–	–	–	–	X	–	3
*Qualitative feedback*							
Willingness continue using BEDDA	–	–	–	–	X	–	3
Willingness pay for BEDDA	–	–	–	–	X	–	3
Improvements suggestions	–	–	–	–	X	–	3
*Breathing exercise Breeze*							
Location	–	–	–	–	–	X	3
Perceived breathing detection accuracy	–	–	–	–	–	X	3
Accelerometer	–	–	–	–	–	X^2^	1,2
Gyroscope	–	–	–	–	–	X^2^	1,2
Magnetometer	–	–	–	–	–	X^2^	1,2
Light sensor	–	–	–	–	–	X^2^	1,2
Ambient temperature sensor	–	–	–	–	–	X^2^	1,2
Humidity sensor	–	–	–	–	–	X^2^	1,2
Pressure sensor	–	–	–	–	–	X^2^	1,2
Step counts since start	–	–	–	–	–	X^2^	1,2
Proximity sensor	–	–	–	–	–	X^2^	1,2
*Smartwatch groups*							
Physical activity	–	–	–	–	–	X^3^	1,2,3
Heart-rate	–	–	–	–	–	X^3^	1,2,3
Heart-rate variability	–	–	–	–	–	X^3^	1,2,3
Sleep duration, length of sleep phases	–	–	–	–	–	X^3^	1,2,3
Oxygen saturation	–	–	–	–	–	X^3^	1,2,3
Respiration rate	–	–	–	–	–	X^3^	1,2,3
Stress level	–	–	–	–	–	X^3^	1,2,3
Skin temperature	–	–	–	–	–	X^3^	1,2,3
Motion-based activity	–	–	–	–	–	X^3^	1,2,3
Steps	–	–	–	–	–	X^3^	1,2,3

Intervention days are repeated measures collected over each day when completing the daily trip. ^1^Each day one of three dimensions (mood, agitation, anhedonia) is used. X^2^ Only while Breeze is used. X^3^ Only in the smartwatch group

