**Fig. 8 Fig8:**
[figure not shown]
Experimental Design. Experimental design of the study. *Note*: T_0_: Assessment at baseline for the control group only. T_1_: Start intervention with start interaction and assessment. T_2_: Half-time intervention with half-time interaction and assessment. T_3_: End of intervention with final interaction and assessment. Intervention: Daily engagement in the intervention consists of interaction with the conversational agent, Breeze, providing assessments, and receiving daily wisdom. Figure created by [name] as part of his employment at the Center for Digital Health Interventions

Participants assigned to the waitlist control group (WG_sw_ and WG_nsw_) will respond to baseline assessments (T_0_) on day 1 and 15 (corresponding to T_1_ and T_2_ in the intervention groups). On day 30 (T_3_ for the intervention group) the control group will start the intervention part of the study. The control group participants will be informed about the assessments, and the study starts through a notification on their smartphones. Participants in the control group will then complete the same intervention as the intervention group including the initial, half-time, and final assessment.

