#### Recruitment, inclusion criteria, exclusion criteria

A highly relevant group that shows alarming rates of symptoms of subclinical [80–83] and clinical depression are undergraduate [84], graduate [85], and Ph.D. students [86]. Our study aims at this population by recruiting participants from Swiss universities with no or subclinical symptoms of depression and anxiety. To increase the diversity of our sample, we plan to recruit participants from the general population as well. We will recruit participants via mailing lists of universities, social media, and other communication channels such as flyers and advertisements. Since participants may know each other spill-over effects could occur.

Participants must be at least 18 years old, not pregnant, not diagnosed with Asthma, COPD, or other respiratory conditions, and should be willing to invest approx. five minutes of their time per day for 30 days. We will use the 9-item version of the Patient Health Questionnaire Short Version (PHQ-9, [44]) for screening purposes to determine the severity of depression. We will also use the 7-item version of the General Anxiety Disorder Questionnaire (GAD-7, [87]) to assess the severity of anxiety. Participants with scores greater than 15 (more than mild symptoms) in either screening instrument will be excluded and directly referred to a mental health hotline for the general public and mental health services of universities. We will also exclude participants responding with “several days (+1)”, “more than half the days (+2)”, or “nearly every day (+3)” to the question of the PHQ-9 assessing suicidal or self-harm ideation, and we advise the participant to seek professional help immediately. We will not use minimal cut-off scores to exclude participants because it is difficult to determine at which point a participant shows sufficient symptoms to benefit from the intervention. Additionally, we expect a selection effect due to the advertisement content focusing on improving symptoms and severity of depression (e.g., one of the outlined potential benefits is “reduce stress”).

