For the second objective, we will proceed in a comparable matter. However, the dependent variables in these models are the symptom severity assessed by the PHQ-9 (depression), GAD-7 (anxiety), and TICS (stress). The independent variables remain the same (voice, breathing, physiological) with a potential extension of using the developed symptom markers from the second objective as additional independent variables. Due to only three assessment times (T_1_, T_2_, T_3_) resulting in three measurements for each participant, we will not be able to develop intra-subject models but will focus on generalizable models for the entire population. Similar to the second objective, we will also infer whether voice and breathing are complementary or alternative markers using a triangulation approach [95].

For the third objective, the estimation of efficacy, we differentiate between proximal and distal outcomes. We based this analysis on a the micro-randomized trial as introduced by Klasnja et al. [59]. However, we have the limitation that the outcomes measured are randomized and not the component. Therefore, we will use Generalized Estimating Equations (GEE; e.g., [96, 97]) to analyze the changes in proximal outcomes. Distal outcomes are the symptom severity changes as determined by the PHQ-9 (depression), GAD-7 (anxiety), and TICS (stress). As stated above in the section regarding sample size estimation, the primary distal outcome is symptom severity of depression. Due to this focus, our first analysis will be a two-way mixed ANOVA (2 groups $$\times$$ 3 measurement times). To investigate post-hoc, whether other factors such as belonging to the smartwatch group, age, and gender have an impact on a potential reduction of severity, we aim to use mixed effect linear regression (hierarchical groups such as intervention and smartwatch vs. no-smartwatch groups). In later analyses, we will investigate intercorrelations between the different dependent variables (PHQ-9, GAD-7, TICS) using a two-way mixed MANOVA (2 groups $$\times$$ 3 measurement times $$\times$$ 3 outcomes). We may compute additional MANOVAs comparing theoretically or empirically connected physiological outcomes to the three distal outcomes if physiological data allow such analyses.

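### Table 2 collects age and gender only at T1, which falls on about day 30 for the waitlist, so early waitlist dropouts lack these covariates while intervention participants lost after their first session have them

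*Protocol article*

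**What the plan says.** In the protocol article, Measurements and assessment times, the text lists age, gender, student type, education, and occupation or field of study, and says they are collected "through open and multiple-choice questions at the start of the study". Table 2 in that section has columns for Screening, T0, T1, T2, T3 and Daily. Its demographics row reads "Demographics – – X": a dash at Screening, a dash at T0, and a mark at T1 alone.

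The note to Fig. 8 defines T0 as the baseline of the control group and T1 as the start of the intervention. Under Study design, T1 is the first interaction for the intervention groups. The waitlist is assessed on days 1 and 15, and on day 30 "the control group will start the intervention part of the study". The Fig. 9 caption instead puts the waitlist's T1 two weeks after T0.

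Under Planned analysis, third objective, a post-hoc mixed-effects regression is to examine whether "belonging to the smartwatch group, age, and gender have an impact on a potential reduction of severity".

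**The concern.** For the intervention groups the sentence and the table agree, because T1 is their study start. For the waitlist they do not: the study starts at T0, and the table defers demographics to the end of the control period.

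The randomised comparison runs over that period. Age and gender should be recorded at the same point after allocation in both arms, before dropout can affect who supplies them. As printed, whether a participant has these covariates depends on both arm and dropout. A mixed-effects model can normally use people with partial follow-up, but a standard fit discards anyone with a missing covariate. Here those discarded after giving baseline outcomes would be waitlist participants who left early. A table comparing the arms on age and gender would have the same gap.

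The gap would also be hard to close later. Enrollment and allocation describes anonymous data collection, and Incentive mechanism says no personal information is held, so asking dropouts for their age and gender afterwards looks infeasible.

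**Working it through.** The protocol gives no figure to reproduce on this point. The check is a reading of the schedule by arm, followed by simple arithmetic.

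**Step 1. Schedule by arm** (Study design, Fig. 8 text, Table 2)

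| | Intervention groups | Waitlist groups |
|---|---|---|
| First distal outcomes in the study (PHQ-9, GAD-7, TICS) | T1, first interaction | T0, day 1 |
| Next assessment | T2, day 15 | day 15 |
| Demographics under Table 2 | T1, first interaction | T1, day 30 |

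**Step 2. Who lacks age and gender, as printed**

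- Waitlist, completes T0 and leaves before day 30: baseline outcomes and possibly day 15, but no age or gender.
- Waitlist, leaves after T1: has both.
- Intervention, leaves after the first interaction: has both.
- Intervention, allocated but never completes the first interaction: has neither demographics nor in-study outcomes.

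The asymmetry therefore lies among people who gave at least one in-study outcome assessment. In the intervention arm all of them have age and gender. In the waitlist arm those lost before day 30 do not.

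**Step 3. Size**

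Inputs:
- Waitlist size: Table 1 plans 25 + 75 = 100. The sample size section aims to enrol 220, which is 220 / 2 = 110 per arm if split equally. Both are used.
- Dropout: the sample size section expects about 20%, not divided by arm or by time.
- Share of the waitlist lost after T0 and before day 30: not stated. Assumed range 5% to 20%; the top corresponds to all the expected dropout falling in the waiting period.

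Formula: number affected = waitlist size × share lost before day 30.

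| Share lost before day 30 | Waitlist 100 | Waitlist 110 |
|---|---|---|
| 5% | 5.0 | 5.5 |
| 10% | 10.0 | 11.0 |
| 20% | 20.0 | 22.0 |

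The range is about 5 to 22 people.

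**Step 4. Sensitivity to the Fig. 9 caption**

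If the waitlist's T1 came two weeks after T0, the window would be shorter and fewer people would be affected. The gap would remain, because demographics would still follow T0. The caption and the Study design text have to be reconciled in any case.

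**Step 5. After the change**

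With demographics marked at waitlist T0 on day 1, everyone who completes the first in-study assessment in either arm has age and gender. The number affected by this mechanism falls to 0.

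**The case against.** The strongest reply is that little depends on this.

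- **The primary analysis is untouched.** It is a 2 × 3 mixed ANOVA without covariates. A conventional complete-case version would drop a waitlist participant with no third measurement anyway. This stands: the harm is confined to the post-hoc regression and the description of the arms at baseline.
- **The intervention arm has a gap too.** Those allocated who never open the app also lack demographics under Table 2. This stands, so the problem is not exclusive to the waitlist. It does not remove the asymmetry among people who supplied outcome data.
- **The size is assumed.** The 20% dropout is not split by arm or time, and the waiting period asks for only two assessments, so loss then may be low. This stands, and is why the range starts at 5 and is labelled as an assumption.

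A reader might draw a stronger inference. Table 2's screening entry is "Pregnant, Resp., Card., mental disease", with PHQ-9 and GAD-7 also marked at screening and no age item, although "Participants must be at least 18 years old". It is tempting to conclude that a minor on the waitlist would be found only after 30 days. The article does not support that. Age is a condition of participation, and Enrollment and allocation has an online survey settle eligibility before anyone is allocated. Table 2 is presented as an overview, and its screening rows also leave out other criteria, such as current psychotherapy or psychopharmacological treatment. A missing entry there does not show that the survey omits age.

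**Conclusion.** The point holds in a limited form. The sentence and Table 2 disagree for the waitlist arm, and followed as printed the table creates a gap in age and gender that depends on arm and on dropout. It affects the post-hoc regression and the baseline comparison, not the primary ANOVA and not, on the evidence here, the age check at enrolment.

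The number affected equals the waitlist loss between T0 and day 30. At an assumed 5% to 20% of 100 to 110 people, that is about 5 to 22. The estimate rests on the day-30 start in the Study design text and on a dropout split that the protocol does not give. It is worth correcting before recruitment because anonymous collection makes later recovery unlikely and the correction is small.

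**What to change.** 1. In Table 2, mark demographics at T0 for the waitlist and keep T1 for the intervention groups. Add a note that the waitlist answers once, on day 1, because the Study design text applies the T0 label to both day 1 and day 15.
2. Reword the sentence above Table 2 to match: demographics at the first in-study assessment of each arm, T1 for intervention and T0 on day 1 for waitlist.
3. Reconcile the Fig. 9 caption with the Study design text on when the waitlist's T1 falls.
4. If the website survey already asks age, show it in the Screening column of Table 2.
5. Optionally, ask eligible respondents for age and gender in the website survey. This would also cover people allocated who never open the app. It is useful only if survey answers can be linked to app records, which the article does not describe.

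**Cost.** Items 1 to 4 move a few existing questions earlier for one arm and correct the text. Item 5 adds a few questions before allocation and needs a link compatible with anonymous collection.

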**Method:**

Participants will interact with the digital intervention BEDDA consisting of a scripted conversational agent, the slow-paced breathing training *Breeze*, and actionable advice for different symptoms. The intervention comprises 30 daily interactions to be completed in less than 45 days. We will collect self-reports regarding mood, agitation, anhedonia (proximal outcomes; first objective), self-reports regarding depression severity (primary distal outcome; second and third objective), anxiety severity (secondary distal outcome; second and third objective), stress (secondary distal outcome; second and third objective), voice, and breathing. A subsample of 25% of the participants will use smartwatches to record physiological data (e.g., heart-rate, heart-rate variability), which will be used in the analyses for all three objectives.

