### Study design

Figure 8 shows the experimental design of the study. The study will run for 60 days, and participants will be randomly (using an algorithm on the recruitment website) allocated to one of four groups we listed in Table 1: intervention with smartwatch (IG_sw_), intervention without smartwatch (IG_nsw_), waitlist with smartwatch (WG_sw_), waitlist without smartwatch (WG_nsw_). The intervention part of the study will run for 30–45 days, depending on how many days the participant needs to finish the required 30 once-per-day guided interactions (described below). Participants allocated to the intervention group (IG_sw_ and IG_nsw_) will start the experiment first. In their first interaction (T_1_), they will receive the study information, give written informed consent via the app (type of content approved by the ethics committee), complete the initial assessment, receive a tutorial on how to use the app, and complete a training with Breeze for the first time. Participants allocated to the waitlist group (WG_sw_ and WG_nsw_) will complete the baseline assessment (T_0_) but will not yet start using the app for another 30 days. In these first 30 days, participants in the intervention group will interact daily with BEDDA. This interaction includes dialogues with the conversational agent, answering questions before and after Breeze, and conducting breathing training with Breeze. Each day, they can also choose whether they want to receive daily wisdom matching the symptom of the day. Additionally, the conversational agent moves the story further each day, and the app uses gamification elements to illustrate progress. On day 15 of the intervention, participants allocated to the intervention group will respond to the half-time assessment questions and on day 30, participants in the intervention group will respond to the final assessment.

**Table 1 Tab1:** Groups included in the study

Group	Treatment	Smartwatch	Planned N
IG_sw_	Intervention	Yes	25
IG_nsw_	Intervention	No	75
WG_sw_	Waitlist	Yes	25
WG_nsw_	Waitlist	No	75

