#### Enrollment and allocation

Interested respondents will complete the initial assessment using an online survey to determine whether they can participate in the study. In this survey, we will also ask eligible participants whether they would be able to pick up the smartwatch from an external institute and be willing to provide the smartwatch data for the duration of the study. Sending smartwatches to participants is not feasible due to requirements from the Cantonal Ethics Commission (Ethics Commission of the Federal State of Zurich, Switzerland) regarding anonymous data collection. Eligible respondents will be enrolled in the study and randomly allocated to either the intervention or waitlist control group using an algorithm on the website (www.bedda.me). If participants are interested in using a smartwatch, it is randomly decided whether they receive a smartwatch or not. Participants not allocated to the smartwatch group will receive instructions on downloading and installing the BEDDA app on their own. Participants assigned to the smartwatch group will receive instructions on how to book an appointment at an external organization to pick up their smartwatches. An individual from the external organization will help participants to install the app on the participantsâ€™ smartphones and enter the key of the smartwatch in the study app. We will collect no personal data during this process and cannot associate any personal data with the collected data.

Usually, blinding participants and staff is complex in most digital health intervention studies. Participants can easily realize if they are in the intervention group that uses a form of digital therapeutic or if they are in a control group (e.g., receiving standard of care or a sham intervention such as printed health information). However, we aim to address this problem by providing installation instructions for all groups after recruitment and only disclosing the intervention’s start time via a notification of BEDDA. However, the smartwatch groups will have a clear indication that they are in one of the smartwatch groups (intervention or waitlist). Still, we will neither disclose the allocation to the intervention or waitlist group to staff or participants in the smartwatch groups.

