#### Proximal and distal outcomes

Following our conceptual model, we measure proximal and distal outcomes. Proximal outcomes are the symptom changes and physiological data changes (e.g., HRV, physical activity, sleep) due to the daily interactions, while distal outcomes are the symptom severity changes over the course of the intervention. For the investigation of efficacy, we use both proximal outcomes (daily reported symptoms) and distal outcomes (symptom severity changes).

For the daily measurements (i.e., proximal outcomes) before and after interacting with Breeze, we use the Multidimensional Mood State Questionnaire (MDMQ) [88, 89], which has the three dimensions mood, agitation, or anhedonia, and two versions (Version A and B). We will infer one of the dimensions using the two versions (one before and one after interacting with the main component Breeze) at each daily interaction. For example, on a given day, the randomly chosen dimension is mood. Then, another draw determines that the questions from version A should be used to measure mood before Breeze. In turn, the questions from Version B are used to measure mood after Breeze. To ensure equal distribution of the daily drawn dimensions and versions, we use a block design consisting of the six question sets (Mood_A_, Mood_B_, Agitation_A_, Agitation_B_, Anhedonia_A_, Anhedonia_B_) and draw from this set until each was drawn once before starting with a new block for the following six days.

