#### Smartwatches

Participants in the smartwatch groups (intervention and waitlist) will receive a smartwatch (Garmin Vívosmart 4 Smartwatch, Garmin International Inc., [name]) at the start of the study. The measurements recorded by the smartwatch are heart-rate and heart-rate variability (via inter-beat-intervals), oxygen saturation, respiration rate, motion-based activity (3-axis accelerometer), stress level, sleep, skin temperature, and steps.

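### Table 2 conflicts with the text on whether waitlist smartwatch data exist before the app starts, and the analysis section does not commit to the one randomised comparison possible for the watch outcomes

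*Protocol article*

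**What the plan says.** **Who gets a watch.** Table 1 (Study design) plans 25 watch users in the waitlist arm, "WG_sw_ Waitlist Yes 25", and 25 in the intervention arm. The Abstract says "A subsample of 25% of the participants will use smartwatches to record physiological data". The Smartwatches section says "Participants in the smartwatch groups (intervention and waitlist) will receive a smartwatch" and places this at the start of the study. Enrollment and allocation asks eligible respondents whether they would "be willing to provide the smartwatch data for the duration of the study".

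**When watch data are scheduled.** Measurements and assessment times lists the assessment times and ends the list with "and during each daily interaction (Daily". In Table 2 all ten watch rows are marked in that column alone, with dashes at T0 to T3, and all ten are tagged to objectives 1, 2 and 3. The table note reads "Intervention days are repeated measures collected over each day when completing the daily trip". Study design gives the waitlist arm no app use for its first 30 days.

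**What the data are for.** Proximal and distal outcomes states: "Proximal outcomes are the symptom changes and physiological data changes (e.g., HRV, physical activity, sleep) due to the daily interactions". Planned analysis says that generalized estimating equations will be used "to analyze the changes in proximal outcomes". Its closing sentence on objective 3 says that further MANOVAs relating physiological to distal outcomes may be computed if the data allow.

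**The concern.** Two things do not fit together.

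First, the schedule. Read as printed, Table 2 and its note give the waitlist group no watch data until its own daily trips begin. The enrolment and smartwatch sections imply data from study start. If those who set up data capture follow the table, the control-period recordings may not be retrieved, and they cannot be recovered later.

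Second, the analysis. Planned analysis itself concedes that, within the intervention, the symptom measured each day is randomised and the component is not. Change within the intervention period therefore contains no randomised contrast for BEDDA. For heart-rate variability, sleep and activity it is a before-after change, open to the novelty of wearing a watch, to season and to the academic calendar. The mood questionnaire and the audio cannot supply a control series during the wait, because they are tied to the daily trip or to Breeze. The watch can, because it records passively in both arms over the same days. The plan has this comparison within reach but does not commit to it.

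**Working it through.** **1. Reproduce the plan's own figures.** Table 1: 25 + 75 + 25 + 75 = 200 participants. Watch users: 25 + 25 = 50, and 50 / 200 = 25%. This matches the Abstract.

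**2. Set the passages side by side.**

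| Place | Waitlist watch data during the wait? |
|---|---|
| Table 2, Daily column and note | None scheduled, if read literally |
| Table 2, T0 column (a waitlist-only time, per the Fig. 8 legend) | Dash on all ten watch rows; marked for PHQ-9, GAD-7, TICS and chatbot reaction time |
| Table 2, footnote on watch rows | Restricts by group, silent on time |
| Enrollment and allocation | Yes, whole study (60 days in Study design) |
| Smartwatches | Watch in hand from study start, both groups |

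The T0 dashes are weak evidence by themselves, because the watch rows also have dashes at T1 to T3. The conflict rests on the definition of Daily and on the note.

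**3. Size of the control window.** Person-days = number of waitlist watch users × days waited.

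- 30-day wait (Study design): 25 × 30 = 750. After the stated dropout of about 20%, 20 × 30 = 600.
- Two-week wait (Fig. 9 legend): 25 × 14 = 350. After dropout, 20 × 14 = 280.
- Under a literal Table 2: 0 waitlist person-days, against up to 750 in the intervention watch group over its first 30 days.

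**4. Precision of the comparison.** Assume one value per person, two-sided alpha 0.05, 80% power and equal arms. The article does not state whether its alpha is one- or two-sided.

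Normal approximation: d = (1.960 + 0.842) × √(2/n).

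- n = 25: 2.802 × 0.2828 = 0.79. With the noncentral t distribution, 0.81.
- n = 20: 2.802 × 0.3162 = 0.89. With the noncentral t distribution, 0.91.

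Half-width of the 95% confidence interval in standard-deviation units: t × √(2/n).

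- n = 25 (48 df): 2.011 × 0.2828 = 0.57.
- n = 20 (38 df): 2.024 × 0.3162 = 0.64.

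At the article's planning effect of d = 0.225, power is about 12% with 25 per arm and 11% with 20. Repeated daily values or baseline adjustment could improve on this. The article gives no correlations from which to say by how much.

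**5. What the analysis section commits to.** The one firm method for proximal outcomes is generalized estimating equations on change, with no arm term mentioned. The physiological MANOVA follows a two-group MANOVA in the text, so a two-group version may be intended, but it is conditional and relates physiological to distal outcomes. Neither names the intervention and waitlist watch groups over the waiting period.

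**The case against.** The strongest reply is that the note is being read too literally. The phone-sensor and audio rows carry a footnote limiting them to Breeze use. The watch rows carry a different one that limits by group only. Sleep duration and sleep phases cannot come from a trip of about five minutes, so for these rows Daily probably means daily frequency. The enrolment text covers the waiting period. This stands. It makes continuous recording the likelier intention, and it also means that Table 2 does not say what is intended.

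A reader might go further and infer that watch data are recorded only on trip days and that the randomised control is lost. The documents do not support that: the request for data throughout the study contradicts it, and nothing says that other data are discarded. Nor do they support the inference that skipped-trip days drop out and tilt the series towards good days. No such exclusion is stated, and no direction could be documented.

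A second reply is that naming a secondary physiological contrast is commonly left to the analysis plan. In part this stands, and silence alone would be no finding. But the article does print the schedule and the method for proximal outcomes, and the point is directed at what they say.

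Third, the primary outcome is untouched and the comparison is weak. Both are true. They limit the point to a secondary estimate.

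**Conclusion.** The point holds as an internal inconsistency together with a missed commitment. Table 2 and its note conflict with the enrolment and smartwatch sections on whether the waitlist watch group contributes data before its intervention starts. Whichever is meant, the analysis section does not commit to the only randomised contrast available for heart-rate variability, sleep and activity, although these are named as proximal outcomes and tagged to the efficacy objective.

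The size is modest. Up to 750 waitlist person-days are in question if the wait is 30 days, and 350 if it is two weeks. The resulting comparison has 80% power only for d of about 0.81 (25 per arm) or 0.91 (20 per arm), so it would yield an estimate with wide limits. These figures assume that Table 1 numbers are reached, 20% dropout in the second case, a two-sided test and one summary value per person. The PHQ-9 analysis by randomised group is not affected.

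**What to change.** - **Table 2 and its note:** state that watch measures are collected on every calendar day from pick-up in both smartwatch groups, including the waiting period and days without a trip. This brings the table into line with the enrolment and smartwatch sections.
- **Planned analysis, third objective:** name intervention versus waitlist smartwatch groups, over the concurrent waiting period, as the efficacy comparison for heart-rate variability, sleep and activity. Report it as a secondary estimate with confidence limits. Label change within the intervention period in these measures descriptive.
- **Length of the wait:** Study design says 30 days and the Fig. 9 legend says two weeks. These must be reconciled, because the comparison window depends on them.

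The cost is wording plus processing of more watch data. No extra watches are needed, and the agreement sought at enrolment already covers the whole study. The documents do not say how consistently watches will be worn during the wait, so wear time should be reported by group. The low precision remains and should be stated.
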